### 10.5.3 Withdrawals due to COPD exacerbations

Participants with exacerbation of COPD may remain in the trial, and continue to take the trial medication. However if the PI or clinical team feel there is an over-riding clinical need for withdrawal (e.g. intubation) the participant will be withdrawn. Participants who are required to stop trial medication for more than 3 days must be withdrawn. The use of systemic steroids or antibiotics will be recorded at each trial visit. Patients with an exacerbation of COPD (defined as requiring systemic corticosteroids) within 4 weeks of the last treatment visit V9 will be excluded from the primary analyses.

If a participant is withdrawn due to an exacerbation, the exacerbation section and AE/SAE section of the eCRF must be completed and the participant should be followed until resolution of exacerbation.

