### Key

^ The 45 day screening period may be extended if patients have an exacerbation that requires steroid or antibiotic use. This period will be extended by at least the equivalent time of steroid use added onto the 45 day period or up to the discretion of the PI where clinical judgement is required.

‡ Patients who have failed screening because of changes to trial inclusion/exclusion criteria or did not attend screening due to medical reasons (i.e. an exacerbation) and their medical status has now changed may be rescreened if they are keen to participate in the trial and happy to undergo a repeat screening, at the discretion of the PI and based on clinical judgement

‡ Patients who have attended the imaging visit but do not progress within 14 days onto the trial due to the necessity to investigate abnormalities on the PET-CT / MRI scan may be considered for subsequent entry onto the trial without undergoing a repeated imaging visit, if performed within a reasonable timeframe, and at the discretion of the PI and based on clinical judgement.

\* Fixed between the dates specified (unless file noted for a specific reason) \*\* ± 96 Hours or as indicated

All the above mentioned procedures as per key can take place ± 96h or as indicated. V8, the FDG-PET/CT and MRI imaging visit can occur at any time between Days 105-111. V9 can occur any time from Day 109-112. However, if there is a specific reason why this may not occur, the deviation will be logged in the Trial File. In some cases, the FDG-PET/CT and MRI scans (Imaging Visits 2 and 8) will occur on the same day but it is very likely that scans be done on separate visits during the intervals indicated above. In the event LFT abnormalities are seen, LFT monitoring may need to occur more frequently, as determined by the investigator and medical monitor.

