18. Women of childbearing potential are excluded from this trial. Women must be of non-childbearing potential [i.e. either postmenopausal or documented hysterectomy and/or bilateral oophorectomy – tubal ligation is not sufficient]. For the purposes of this trial, postmenopausal is defined as being amenorrhoeic for greater than 2 years with an appropriate clinical profile, e.g. age appropriate, history of vasomotor symptoms.  
  
An unwillingness of male patients to abstain from sexual intercourse with pregnant or lactating women; or an unwillingness of the patient to use a condom/spermicide in addition to having their female partner use another form of contraception such as an intrauterine device (IUD), diaphragm with spermicide, injectable progesterone, sub-dermal implants or a tubal ligation.
19. Any medical history or clinically relevant abnormality that is deemed by the principal investigator and/or medical monitor to make the patient ineligible for inclusion because of a safety concern.
20. Use of systemic corticosteroids (oral or IV) 4 weeks prior to Visit 2 (Day -14 to -1).

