### **11.11 Concomitant Medications and Non-Drug Therapies**

All concomitant medications will be recorded in the eCRF.

Participants taking systemic steroids (IV or Oral) within 4 weeks of the final treatment visit (V9) will be excluded from the primary analysis.

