### **V8 Imaging visit (Days 105-111):**

- The repeat FDG-PET/CT scan can take place any day between Days 105-111.
- The repeat MRI scan (for those participants this applies to) can take place any day between Days 105-111.
- Adverse event assessment.

A clinical report will be generated for the post dose scans as part of Clinical Governance.

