## 16.2 Analysis Populations

**Inflammation Population:** All participants who provide baseline (V3) and post-dose (V9) scans but excluding those taking systemic steroids within 4 weeks prior to V9 will be included in the primary statistical analysis population. This population will be used in the evaluation of inflammation data.

**Safety Population:** All participants who receive at least one dose of trial drug will be included in the safety population. Randomized participants will only be excluded if there is clear documented evidence of failure to take any trial medication. Participants in the

Safety Population will be classified according to the treatment received. All safety summaries will be based on the Safety Population.

Pharmacodynamic Population: All participants who provide baseline and V8 pharmacodynamic (PD) data will be included in the PD population. This population will be used in the evaluation of PD.

MRI Population: All participants who provide baseline V3 and V9 MRI data will be included in the MRI population. This population will be used in the evaluation of MRI data.

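### The 4-week steroid exclusion is counted from V9 although the post-dose scans are at V8, and the protocol's sections disagree on which analyses it covers

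*Protocol*

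**What the plan says.** Three places in the protocol set an end-of-treatment steroid exclusion, all tied to V9.

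- Section 10.5.3: patients with an exacerbation requiring systemic corticosteroids "within 4 weeks of the last treatment visit V9 will be excluded from the primary analyses".
- Section 11.11: participants taking systemic steroids "within 4 weeks of the final treatment visit (V9) will be excluded from the primary analysis".
- Section 16.2, Inflammation Population: membership depends on paired scans, described as "All participants who provide baseline (V3) and post-dose (V9) scans". The steroid limit follows later in that definition: "excluding those taking systemic steroids within 4 weeks prior to V9 will be included in the primary statistical analysis population".

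The schedule puts the scan elsewhere. In Section 12.1.5 under V8, "The repeat FDG-PET/CT scan can take place any day between Days 105-111", and the same days apply to the repeat MRI. Table 7 gives Day 107 as the nominal V8. The key to the flow chart in Section 6 says "V9 can occur any time from Day 109-112"; Section 12.1.5 prefers Day 112. V9 has no scan but includes FMD, which Section 9.6.1 lists among the primary endpoints.

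At entry, Section 10.2 ties the matching 4-week rule to the baseline imaging visit: "Use of systemic corticosteroids (oral or IV) 4 weeks prior to Visit 2 (Day -14 to -1".

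On populations, Section 16.2 says "All participants who provide baseline and V8 pharmacodynamic (PD) data will be included in the PD population" and adds no steroid exclusion there or in the MRI Population. Section 16.6 then runs the primary analyses on the PD population.

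**The concern.** A steroid-free window protects a measurement only if it ends at that measurement. Here it ends at a different visit, usually some days later. Two errors follow under the protocol's own 4-week criterion. A scan already taken can be discarded because of an exacerbation that came after it. A scan can also be kept although a steroid course ended within the 4 weeks before it. The first error is the less comfortable one: it removes a measured outcome because of a later, post-randomisation event that an anti-inflammatory drug could itself influence.

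The second issue is scope. The sections give different answers on whether the exclusion applies to FMD and MRI. If that is not settled in advance, membership of a primary analysis can be chosen after the data are seen.

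**Working it through.** **1. Offset between the two visits.** V8 may be any of 7 days (105-111) and V9 any of 4 (109-112), giving 7 × 4 = 28 day-pairs. V9 − V8 runs from 109 − 111 = −2 to 112 − 105 = +7; nominally it is 112 − 107 = 5. V9 follows V8 in 22 pairs, coincides in 3 and precedes it in 3.

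**2. What each window covers.** Count 28 days up to, but not including, the assessment day.

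| V8 | V9 | Window used (before V9) | Window before scan | Before scan but not covered | Covered but on or after scan day |
|---|---|---|---|---|---|
| 107 | 112 | 84-111 | 79-106 | 79-83 | 107-111 |
| 105 | 112 | 84-111 | 77-104 | 77-83 | 105-111 |
| 111 | 112 | 84-111 | 83-110 | 83 | 111 |
| 111 | 109 | 81-108 | 83-110 | 109-110 | none |

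In the second row, a course that ended on Days 77-83 (22 to 28 days before the scan) leaves the participant in, and a course first given after the scan takes the participant out. In the last row, steroids given on the two days just before the scan escape a rule that looks only at the time before V9. That rule also counts Days 81-82, which lie more than 28 days before the scan.

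**3. Direction of the window.** Sections 10.5.3 and 11.11 say *within 4 weeks of* V9; Section 16.2 says *prior to*. The looser form can be read as running forward from V9. The V10 follow-up (Days 120-126) has a concomitant medication check, so courses after V9 would be on record.

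**4. Expected numbers.** The documents give no rate of steroid courses, so 0.5 to 2 per patient-year is assumed. Expected participants of 60 with a course starting in d days = 60 × (1 − exp(−rate × d/365)). At a steady rate, the same figure approximates courses ending in d days.

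| d | 0.5/year | 1/year | 2/year |
|---|---|---|---|
| 5 | 0.41 | 0.82 | 1.62 |
| 7 | 0.57 | 1.14 | 2.26 |
| 28 | 2.26 | 4.43 | 8.53 |

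The first two rows give the misclassification in each direction. The last row illustrates how many participants have an FMD status that depends on which section is followed.

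**5. Precision, for scale.** Section 16.4 states a 90% chance of a half-width of 0.17 or less, with SD 0.3 and 30 per arm. Half-width = q × s × √(2/30), with 58s²/0.3² chi-square on 58 df. With q = 1.96 the chance is 90.8%, which reproduces the stated figure; with the t quantile it is 86.1%. If one scan per arm were lost and not replaced (29 per arm), the chances would be 86.7% and 80.8%.

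**6. Scope, side by side.**

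- 10.5.3 and 11.11: exclusion from the primary analyses or analysis, not limited to scans. Read literally, this includes FMD.
- 16.2: exclusion written only into the Inflammation Population, which it also calls the primary one.
- 16.6: primary analyses on the PD population, with no exclusion. That population is defined by V8 data, and FMD is not measured at V8.

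These cannot all be followed.

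**The case against.** The strongest reply is that V9 is a sensible single cut-off. It carries FMD, arterial stiffness, fibrinogen and hsCRP, and the inflammation data for which the Inflammation Population is used may include those blood markers. For V9 measures the anchor does fit; for PET and MRI it does not.

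The entry comparison is also less clean than it looks, because at V3 the protocol checks again for systemic steroid use since V1. That softens the contrast but does not move the end-of-treatment window.

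Recruitment continues until about 60 participants meet the primary population definition (Sections 9.3 and 16.4), and withdrawn participants may be replaced (Section 10.5). Lost precision is therefore largely recoverable. Selection on events after the scan is not. The trial is exploratory and focused on estimation, which limits the harm.

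Three stronger readings are tempting, and the documents do not support them:

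- A reader might infer that steroid-exposed FMD values certainly stay in. Sections 10.5.3 and 11.11, read literally, take them out. What exists is a contradiction.
- A reader might infer that the V9 anchor is unrelated to wrong visit labels. That is fair for 10.5.3 and 11.11, which correctly name V9 as the last or final treatment visit. It is not established for 16.2, which itself calls the scans V3 and V9; the anchor there may follow from that label.
- A reader might infer that the kept scans are demonstrably altered by steroids. No document shows a residual effect 22 to 28 days after a course. They fail only the protocol's own 4-week test. Also, 11.11 and 16.2 turn on taking steroids, so such a participant is kept only if the course had ended before the window opened.

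**Conclusion.** The point holds. The window is attached to V9 while the scans it governs are at V8, a mismatch of 5 days nominally and from −2 to +7 as permitted. It can misclassify participants in both directions. The rule's forward reach and its scope are also stated inconsistently across 10.5.3, 11.11, 16.2 and 16.6.

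The misalignment affects few participants: at the assumed 0.5 to 2 courses per patient-year, about 0.4 to 1.6 of 60 each way at 5 days and 0.6 to 2.3 at 7. The 7-day case is one extreme of the 28 permitted pairs. The day arithmetic is certain; the head-counts rest wholly on the assumed rate. This should be corrected because the rule defines the primary population and the correction is nearly free, not because it threatens the trial's result.

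**What to change.** In Sections 10.5.3, 11.11 and 16.2, reconciled with 16.6:

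- Count the 4 weeks *prior to* the date of the assessment being analysed: the participant's own V8 scan date for PET and for MRI, and the V9 date for FMD and other V9 measures.
- State that steroids first given after an assessment do not exclude that assessment.
- Name each population to which the exclusion applies, and make 16.6 point to the same one.
- Correct the V3/V9 scan labels in 16.2. Correcting those labels alone would leave 10.5.3 and 11.11 unchanged.

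The cost is wording; no treatment or visit changes. A few FMD or MRI datasets that 16.2 now keeps may be excluded. Section 10.5.3 has steroid use recorded at each visit but does not expressly promise dates, so the sponsor should confirm that the eCRF captures start and stop dates.

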## 11 Trial Treatments

### 11.1 Data from Non-Clinical Studies

Losmapimod is a novel p38 MAPK inhibitor which is in clinical development Phase II. For further information concerning data from Non-Clinical studies please refer to the IB.

### 11.2 Clinical Data

#### 11.2.1 Efficacy

After completion of phase I trials in healthy volunteers, Losmapimod 7.5 mg BD was studied in a 12 week randomized clinical trial in COPD patients. Heat shock protein, a downstream effector of p38 MAP kinase was significantly reduced compared with placebo after 4 and 12 weeks of therapy in the group that received losmapimod (ratio of effect of Losmapimod/placebo 0.56, 95% CI 0.43 to 0.73,  $p < 0.001$  at 4 weeks and ratio of effect of Losmapimod/placebo 0.61 95% CI 0.46 to 0.82,  $p < 0.001$  at 12 weeks). Losmapimod significantly reduced plasma fibrinogen by 11% ( $-0.4 \text{ g/L}$ , placebo adjusted mean at 12 weeks  $3.6 \text{ g/L}$ , Losmapimod adjusted mean at 12 weeks  $3.2 \text{ g/L}$ ; ratio of effect of Losmapimod/placebo 0.89, 95% CI 0.83 to 0.96;  $p = 0.002$ ). There was a trend in ratio

of effect for Losmapimod/placebo of 0.81 for IL-6 (95% CI 0.63 to 1.03; p=0.09), 0.83 for IL-8 (95% CI 0.66 to 1.04; p=0.10) and 0.76 for CRP (95% CI 0.55 to 1.06; p=0.10). The administration of Losmapimod resulted in a non-significant increase in post-bronchodilator forced vital capacity (92mL; 95% CI: -5 to 190mL; p=0.06) and non-significant reductions in both residual volume (124mL; 95% CI: -9 to 257mL; p=0.07) and thoracic gas volume (113mL, 95% CI: -20 to 246mL; p=0.09) when compared to placebo (Table 2). There was no effect on inspiratory capacity.

### 11.2.2 Safety and tolerability

Based on the latest data provided by GSK at the time of finalisation of this EVOLUTION protocol, since November 2011:

**Table 2:**

|                                                                                                                               |
|-------------------------------------------------------------------------------------------------------------------------------|
| Approximately 1000 subjects have received at least 1 dose (up to 60mg single dose).                                           |
| Approximately 800 subjects received 7.5mg BD (for up to 3 months).                                                            |
| Approximately 300 subjects have been dosed for $\geq 3$ months.                                                               |
| Approximately 450 subjects are completing dosing in December 2011 in an ongoing 6-month Phase IIb COPD trial (up to 15mg BD). |

This information supersedes data provided in the IB.

The longest duration of dosing in completed studies is 3 months. As above, a trial of 6 months duration completed dosing in Dec 2011 in patients with COPD, at doses of 2.5 and 7.5 mg BD for 6 months, and 7.5 mg BD for one month followed by 15 mg BD for 5 months. No safety concerns have been identified in these trials via review of blinded data in an ongoing fashion.

On-therapy AEs in repeat dose studies in patients have occurred more frequently in Losmapimod vs placebo groups (61% vs 53%), but no concerning trends have been identified with regard to any particular event. The most frequent AE was headache in Losmapimod vs placebo (13% vs 16%). Many of the events were only reported in one instance, making any distinction difficult. Pyrexia was noted more frequently in Losmapimod groups than placebo. Most of the cases were reported in two 28 day studies in neuropathic pain syndromes and many were associated with mild illnesses such as nasopharyngitis and gastroenteritis. These events were mostly classified as mild or moderate and did not result in withdrawal of trial drug.

Liver events as defined by subjects experiencing ALT  $\geq 3$ x ULN have occurred with similar frequency in Losmapimod and placebo treated groups (12 (0.9%) v. 3(0.5%) respectively). Although slightly more cases of ALT elevations have occurred in Losmapimod compared to placebo, most of these cases had confounding factors that could contribute to elevation in transaminases and occurred in a recent trial completed in patients with acute coronary syndrome. All were asymptomatic outside of underlying disease states. There were 2 cases in which LFTs increased after drug had been stopped, but in one case, there was a mixed pattern of LFT increases, and in the other cases, ALT increase occurred weeks after stopping drug, which would be atypical for a drug effect, or with other cases seen with Losmapimod to date. Overall, most of the liver events seem related to confounding factors or underlying disease process, and no definitive liver

safety signal is identified. Liver events continue to monitored closely in all ongoing trials with Losmapimod.

### **11.2.3 Pharmacokinetics & pharmacodynamics**

The predominant route of elimination of GW856553 was via urine (approximately 65% of the dose) with approximately 29% of the dose eliminated via faeces. Elimination of GW856553 was almost exclusively by metabolism with only 2% of the administered dose recovered as unchanged drug in urine and faeces. The principal route of metabolism was via hydrolysis of the cyclopropylamide group to form a pharmacologically inactive metabolite, GSK198602. Absorption of unchanged GW856553 from a solution dose was high based on the low percentage recovery of parent drug in faeces (approximately 2% of administered dose) and the high recovery of drug-related material in urine (65% of administered dose).

After single oral dose administration of 1 to 60 mg GW856553,  $C_{max}$  and area under the plasma concentration time curve ( $AUC_{(0-\infty)}$ ) of GW856553 increased in an approximately dose proportional manner for doses up to 20 mg and less than proportionally from 20 mg to 60 mg. The terminal half-life of GW856553 was approximately 10 hours. After single oral dose administration of GW856553, exposure ( $AUC$ ) was approximately 2-fold higher for metabolite GW198602 compared to parent GW856553.

Steady-state plasma concentrations of GW856553 were achieved 2 to 3 days after initiation of repeat dosing. Slight accumulation (up to approximately 30%, on average) for  $AUC$  and  $C_{max}$  after once or twice daily dosing was observed. Consistent with single dose administration, exposure ( $AUC$ ) was approximately 2-fold higher for metabolite GW198602 compared to parent GW856553.

A high fat meal increased  $AUC$  (~10%) and  $C_{max}$  (~40%) of GW856553 compared to the fasted state. Time to maximum plasma concentration ( $T_{max}$ ) was delayed, on average, by 1 hour when GW856553 was administered with a high fat meal.

In general, systemic exposure appears to be similar in rheumatoid arthritis patients, COPD patients, and patients with dyslipidemia compared to healthy volunteers.

The effect of age on the pharmacokinetics of GW856553 was evaluated after single dose administration of 20 mg GW856553 to 12 elderly patients (age 65 to 75 years) and 12 young patients (age 33 to 52 years). The results indicated that exposure ( $AUC_{(0-\infty)}$  and  $C_{max}$ ) was similar for the two groups.

The effect of gender on the pharmacokinetics of GW856553 was informally evaluated after single dose administration of 20 mg GW856553 to 6 female and 6 male elderly patients. On average,  $AUC_{(0-\infty)}$  and  $C_{max}$  were slightly increased (approximately 25% and 28%, respectively) in the female patients.

Rosuvastatin (a substrate for the organic anion transporting polypeptide 1B1 and breast cancer resistance protein transporters)  $AUC_{(0-\tau)}$  and  $C_{max}$  were modestly increased (30% and 25%, respectively) following administration of rosuvastatin 10 mg once daily and GW856553 15 mg once daily for 14 days compared to administration of rosuvastatin alone. These increases in rosuvastatin exposure are not considered clinically significant.

After administration of GW856553 to healthy volunteers, *ex vivo* production of LPS-stimulated  $TNF\alpha$  and sorbitol-stimulated phosphorylated heat shock protein (pHSP)-27 in whole blood were both inhibited. The pharmacokinetic/pharmacodynamic relationships between GW856553 plasma concentration and LPS-stimulated  $TNF\alpha$  inhibition, and

sorbitol stimulated pHSP-27 inhibition, were adequately described by sigmoid maximum effect ( $E_{max}$ ) models. The estimated maximum inhibition for  $TNF\alpha$  was 78% with an effective concentration 50% ( $EC_{50}$ ) of 9.12 ng/mL. The estimated maximum inhibition for pHSP-27 was 76% with an  $EC_{50}$  of 8.45 ng/mL. Further details may be found in Section 5.2 of the IB.

### 11.3 Dose Rationale

Although there are little clinical dose-response data with Losmapimod that can provide insight on an efficacious dose, in trial MKI101678, the *ex vivo* monocyte expression of  $TNF\alpha$  (LPS treated) and sorbitol stimulated monocytes revealed pHSP27 were reduced by over 50% following 7mg Losmapimod and the inhibitions were generally higher and lasted longer following single dose of 20mg and 60mg of Losmapimod compared to 7mg.

In COPD patients (trial MKI106209) there was evidence of LPS-stimulated  $TNF\alpha$  inhibition following repeat dosing with 7.5mg BD Losmapimod compared with placebo, when adjusted for pre-dose levels on Day 1. Results for the treatment ratios relative to placebo indicated that 7.5mg Losmapimod twice-daily demonstrated a statistically significant increase in inhibition of LPS-stimulated  $TNF\alpha$  at 2 h post-dose on Day 1, at pre- and 2 h post-dose on Day 7, and pre-, 2 h and 6 h post-dose on Day 14 (particularly at 2 h post-dose on each of the days).

Analysis of plasma fibrinogen based on the limited data from the COPD Phase 2a trial MKI102428 showed a trend of greater reduction in fibrinogen with increase in steady state average exposure of Losmapimod in a non-linear form. Additionally, the modeling of *ex vivo* pHSP27 and systemic Losmapimod exposure indicated approximately 30% inhibition at trough and about 60% and inhibition at peak following 7.5mg BD dose.

The 7.5mg BD dose level yielded average (range) AUC and  $C_{max}$  values of 522 ng.hr/mL (291-933 ng.hr/mL) and 41.2 ng/mL (23.7-64.2 ng.hr/mL), respectively. These exposure values are well below those observed when subjects were given a single dose of 60mg Losmapimod (GW856553) as a micronized tablet under fed conditions (1226-2247 ng.hr/mL and 133-335 ng/mL) and this dose was found to be well-tolerated. In addition, the maximum individual AUC value is approximately 9-fold lower than the NOAEL AUC value for the 28 day rat trial and approximately 20-fold lower than the NOAEL AUC value for the 28 day monkey trial.

